## Purpose

The purpose of this research is to reduce the risk of preventable adverse drug events and hospital re-admissions post discharge by testing novel strategies to improve the transmission and reconciliation of medication information at discharge from hospital.

---

## Preventable Adverse Drug Events

Up to a quarter of admissions to acute care hospitals are related to adverse drug events (ADE). ADEs are the 6th leading cause of death at a cost over \$5.6 million per hospital per year. Fortunately, at least 58% of these ADE's are preventable, as they result from incomplete drug information, prescribing or dispensing errors, and overuse or underuse of medications. The convergence of increasingly complex care plans, an aging patient population, and multiple transfers between care settings (long term, acute care, community) account for most of the preventable errors that ultimately result in ADEs. In fact, at admission, 60%-70% of medication histories contain at least one error, the majority of which are errors in omitted medication, and 37% have the potential to cause harm^3-8. Failure to obtain a complete profile of pre-admission medication is responsible for 72% of potential adverse drug events after discharge. An estimated 19% to 23% of patients will have an adverse event within 30 days of discharge, 14.3% will be readmitted, and 70% of these events will be related to prescription medication.

---

## Medication Reconciliation at Discharge

Reconciliation of community-based medications with changes during hospitalization is a critical requirement to reduce the risk of preventable adverse drug-related events during transitions in care. Its importance is evident in hospital accreditation standards in Canada and the United States, which now require implementation of a method for medication reconciliation. Essentially, medication reconciliation at discharge involves two elements: 1) obtaining the community-based drug history of current active medication, and determining which drugs have been stopped, changed, or added during the hospital stay, and 2) communicating information on changes in community-based medication made during hospitalization to the responsible pharmacists and physicians at discharge. In the past few years, considerable experience has accumulated on the challenges of implementing medication reconciliation in a variety of clinical areas and patient populations. A number of critical challenges have been identified that limit effective implementation, particularly in transitions between community and hospital settings.

### *Challenge #1 Obtaining an accurate community-based medication list*

Difficulty in obtaining accurate information about the community-based drug list is one of the greatest challenges in medication reconciliation. In a recent survey of hospital staff, respondents estimated that 87% of admitted patients did not know which medications they took, 80% of the time medication information was not available from alternate sources such as relatives or community-based care providers, and in 63% of admissions, hospital staff were unable to access community-based records. As a result, 46%-67% of unintended discrepancies in medication reconciliation are omitted medications, that is medications that were taken in the community but were neither prescribed at admission nor reconciled at discharge. The most commonly omitted medications are cardiovascular drugs, pain medications, anti-infectious medications, and central nervous system medications such as anti-depressants and sleeping pills. Overall, 23% to 37% of unintended discrepancies between community and hospital medication are considered clinically significant, meaning that there is substantial potential to cause harm. An increasing number of hospitals are employing pharmacists in the emergency department and inpatient units to obtain a complete history of community-based medications. Pharmacists have been shown to be more effective than nurses or medical staff in obtaining an accurate medication history, reducing errors from 323 to 86 per 1,000 prescription orders compared to nurse-taken histories where errors

---

 [www.ahrq.gov/qual/aderia/aderia.htm](http://www.ahrq.gov/qual/aderia/aderia.htm)

 [www.accreditation.ca/uploadedFiles/Knowledge\\_Exchange/Patient\\_Safety/Required\\_Organizational\\_Practices](http://www.accreditation.ca/uploadedFiles/Knowledge_Exchange/Patient_Safety/Required_Organizational_Practices)

were reduced to only 157 per 1,000^33. The superiority of pharmacists in medication history-taking may be related to two aspects of care. First, pharmacists spend an average of 12.9 minutes per patient to take a community-based medication history, 2-3 times longer than medical or nursing staff. Second, pharmacists dispense medication and in general are much more knowledgeable about medication characteristics. This expertise may be particularly useful when patients are attempting to recall their medication, as most patients remember their medications by the colour, shape and general purpose of the pill—“*I take a round orange pill every morning for my blood pressure*” (translation: *Apo-Hydrochlorothiazide 12.5 mg, OD*). Pharmacists may be more likely to identify these medications than medical and nursing staff, who know the name but not usually the colour and shape of the pill. Indeed, a recent pilot study performed in a U.S. Veteran’s Affairs hospital found that the integration of pill image files with medication lists was a useful approach to verify current use with patients.

Although pharmacist deployment in clinical care areas is considered a cost-effective investment in preventing medication errors, pharmacists are conventionally not available on weekends, evenings and nights, nor are community-based pharmacies or office-based practices usually open to transmit information about community-based medications by fax or telephone. As such, recent research has shown that unintended errors in reconciling community and admission medications at discharge are more likely to occur at night-time admission, particularly for elderly patients and those using >4 medications.

New initiatives have been undertaken to use electronic medical records to access information about the community drug profile. Brigham and Women’s Hospital in Boston has shown that retrieval from electronic medical records can identify 65% of current medications. The major limitations of using medication lists in electronic medical records is that many of the listed medications (up to 70%) are no longer being used by the patient as medication lists become out-of-date, and 15.5% of current medications are not listed in the electronic medical record. Moreover, low adoption rates of electronic medical records in Canada and the United States, means that retrieval of community medications from electronic medical records may be a mid to long term solution for effective medication reconciliation.

In contrast, almost all pharmacies in North America have been computerized so that they can manage the on-line adjudication processes of public and private drug insurance programs. Prior research has shown that records of dispensed prescriptions can be used to accurately measure medication adherence. A recent study from the Netherlands also suggests that community pharmacy records can identify up to 97.6% of community-based medications accurately. Although it represents a promising approach, the utility of community-based pharmacy records for medication reconciliation at hospital discharge has not been formally assessed.

### *Challenge #3 Communicating Drug/Dose Changes at Discharge to Community-based Prescribing Physicians and Dispensing Pharmacists*

A substantial proportion of adverse drug-related events occur in hospitalized patients shortly after discharge. It is estimated that 72% of medication reconciliation errors at discharge are due to an incomplete preadmission community drug list, while 26% are due to failures in reconciling the medication history or changes made during the hospital stay with discharge orders. During hospitalization 31% of patients will have changes made in the dose and frequency of medication, 9% will have a medication added or substituted and 4.1% to 8% will have a medication stopped. At the present time, there is no timely and effective mechanism of communicating these changes in medication to the community-based prescribing physician(s) and dispensing pharmacist(s). Most patients fill their discharge medication prescription within the first few days after hospital discharge, far before the discharge summary that summarizes the reasons for hospitalization and changes in medical management has been dictated or transmitted. Indeed, in the majority of admissions, the community-based care team does not receive critical information on the patient's health status and modified treatment plan post-discharge. As a result, the patient's community-based pharmacist(s) needs to determine whether remaining refills on community-based drugs are to be added to the discharge prescription or stopped; and whether the dose prescribed on a discharge medication is to be added or replace the existing pre-admission medication dose. As the community-based profile is typically incomplete, these issues are usually not addressed in the discharge prescription. To add to the challenges of discharge reconciliation, 70% of elderly patients who use many medications are under the care of a number of prescribing physicians and over 40% of patients will use more than one dispensing pharmacy. For all of these reasons, it is not surprising that 17% to 21% of patients will experience adverse drug-related events post-discharge, and that the majority of discrepancies in community and hospital medication reconciliation are related to therapeutic duplication (more than one drug from the same class), dose errors, and omitted medication.

**In summary,** effective implementation of medication reconciliation is essential to reduce preventable adverse drug events occurring at the transitions between community and hospital care. More efficient and reliable methods of obtaining the community drug list are critical to improve hospital staff adherence to the medication reconciliation process and reduce unintended discrepancies in community and hospital medication at discharge. Community-based pharmacy records could be used, particularly if the hospital treatment team could automatically retrieve these records. Adherence to medication reconciliation at discharge will likely be improved by providing an automated order entry process that facilitates re-ordering of hospital and community-based medications at discharge. Moreover, the effectiveness of an electronic medication reconciliation module in reducing adverse drug events may be augmented by interventions to improve the successful transmission of treatment discontinuation and change orders to community-based pharmacists and physicians.

### **Opportunities for Innovative Approaches to Medication Reconciliation in Canada**

In Canada, there are unique opportunities to incorporate innovative solutions into medication reconciliation. As a by-product of our public drug insurance program, each province maintains comprehensive records of all dispensed medication for those insured through provincial drug programs. Moreover, almost all provinces provide a comprehensive drug benefit plan for seniors, the population that is at greatest risk of adverse drug events and most likely to be hospitalized. For over a decade, our group has conducted

research on the potential benefits of providing information on dispensed medication to primary care clinics in Quebec, showing that it reduces inappropriate prescribing, and increases access to information to the most vulnerable populations of patients with the lowest education and the most complex drug management. Community pharmacy records are now being made available to emergency departments in Ontario, B.C., and Manitoba.

Moreover, with Canada Health Infoway, provinces are advancing the capacity to provide unprecedented drug information access to hospitals, community-based pharmacies and physician offices by implementing provincial pharmanets, which will enable access to information on all active and past prescription drugs for all provincial residents, regardless of their insurance status.

## Study Objective

To determine if an electronically-enabled discharge reconciliation intervention that includes:

- 1) electronic retrieval of community drug lists from community pharmacy records,
- 2) reconciliation of community and hospital drugs at discharge, and
- 3) communication of treatment changes to the community-based prescribing physicians & pharmacists

will reduce the risk of adverse drug events (ADEs), ER visits and re-admissions in the 30 days post-discharge compared to usual care.

## Pilot Study Results

To determine if the electronic retrieval of the community drug list would add value to the usual care process, we conducted a pilot study at the McGill University Health Center. To access medications from community pharmacies, we used an integrated drug management system (MOXXI) that our research group had already developed to provide on-line access to the Quebec government prescription database of all medications from community pharmacies. The MOXXI system provides near real-time information (within 24 hrs.) on dispensed prescriptions from the 1,800 community pharmacies in Quebec through a secure virtual private network that links to the prescription claims adjudication system of the government insurer (RAMQ). 135 primary care physicians and specialists and 92,500 patients use MOXXI as part of an on-going research program on the impact of information technologies on the quality of care. In the pilot study, we assessed whether the community drug profile identified missing medication at admission, the value for the treatment team, and the number of community providers who would be affected by a discharge reconciliation and communication intervention. In 91 consecutive patients admitted in 2009, we showed that electronically retrieved community pharmacy records identified, on average, 3 additional drugs per patient. For 21% of patients,  $\geq 5$  drugs were identified (Figure 1).

**Figure 1 Differences in the Community Drug Profile  
ER Medication History vs. Community Pharmacy Records**

[figure not shown]

**Figure 2 ED Nurses and Physicians (n=33) Perceptions of Value and Access**

[figure not shown]

 [www.health.gov.on.ca/en/public/programs/drugs/access\\_drug\\_history/](http://www.health.gov.on.ca/en/public/programs/drugs/access_drug_history/)

Over 90% of physicians and nurses who accessed real-time community pharmacy records believed this information improved the quality and continuity of care (Figure 2). Overall, 72.7% were confident in their ability to use a computer to gain access, even though 29% had limited or no prior computer experience. Access to the community drug profile reduced medication history-taking by 2.5 minutes per patient. Moreover, the challenges for staff to access treatment information for traditional medication reconciliation were substantial as 31% of patients had more than one dispensing pharmacy, most had multiple prescribing physicians, and 14.3% had more than 8 (Table 1).

**Table 1 The Number of Prescribing Physicians and Dispensing Pharmacies for 91 consecutive patients admitted to the MUHC (April-May, 2008)**

| Number of Prescribing Physicians | N (%)      | Number of Dispensing Pharmacies | N (%)      |
|----------------------------------|------------|---------------------------------|------------|
| 1 prescribing physician          | 6 (6.6%)   | 1 pharmacy                      | 60 (69.0%) |
| 2-4 prescribing physicians       | 34 (37.4%) | 2 pharmacies                    | 18 (20.7%) |
| 5-8 prescribing physicians       | 38 (41.8%) | ≥3 pharmacies                   | 9 (10.4%)  |
| ≥9 prescribing physicians        | 13 (14.3%) |                                 |            |

## Study Design

A randomized cluster design will be used to determine if electronically-enabled discharge reconciliation reduces adverse events post discharge. The study population will be patients admitted to medical, surgical, and psychiatric units at the McGill University Health Center. Patients will be stratified by medical, surgical or psychiatric admission, and a cluster randomization approach will be used to allocate the 16 medical, 10 surgical, and 2 psychiatric units to discharge reconciliation and communication versus usual care (Figure 3).

**Figure 3 Stratified Random Cluster Design of Electronically-Enabled Discharge Reconciliation vs. Usual Care**

[figure not shown]

A cluster randomization approach is required to avoid contamination between the two interventions (usual care vs. discharge reconciliation and communication). This is because all medical staff, who are clustered within units, will need to be trained, and provided with on-site support to successfully use computerized order entry to reconcile the community drug list with the in-patient drug list. It will not be possible to randomize patients within a unit without risk of contamination. The primary outcome, adverse drug-related events in 30 days, will be measured by follow-up interview 30 days post-discharge, as this is when post-discharge adverse events occur, and the secondary outcome, re-admission/ER visit, will be assessed by retrieving complete service utilization claims files from the Quebec insurance agency

## Study Population

**Eligibility:** The target population comprises patients who are at risk of preventable adverse drug events during transitions between community and hospital care. This population represents approximately 60% of the 3.1 million patients admitted to hospital each year in Canada, of whom 93,000 to 428,000 are expected to experience an adverse drug event. The study will be conducted at the McGill University Health Centre, a network of teaching hospitals that serve a population of 1.3 million Quebecers from Montreal to James Bay, including a trauma center, two tertiary adult hospitals, a psychiatric facility and a specialized hospital for respiratory disease. Teaching hospitals represent approximately 28% of hospital beds in

Canada, but they treat a higher proportion of complex, vulnerable patients where improvements in medication safety would have the greatest benefit. Patients will be eligible for inclusion in the study population if they are: 1) using prescription medication at admission, 2) covered by the Quebec drug insurance plan, 3) admitted from the community, 4)  $\geq 18$  years old at admission, 5) admitted to a general or intensive care medical, surgical or psychiatric unit, 6) discharged alive. Patients who are cognitively impaired or otherwise unable to provide consent will be included as we have shown that this subpopulation of patients may be at greatest risk of adverse events because of communication problems. Tri-council ethics guidelines deem that this subpopulation should not be excluded from interventions that potentially provide direct benefit to the participant because of the inability to provide informed consent (Article 4.5). For these patients, the family if present, or the medical director of the admitting unit will authorize study participation. Demographic, clinical and health care service use characteristics of the study population will be retrieved from the admission note, and provincial health care administrative databases in the year before admission and in the two months after discharge to characterize the study population, evaluate the integrity of randomization, assess potential biases related to losses to follow-up, and assess re-admission.

*Sample size:* We based our sample size requirements on the primary outcome for discharge reconciliation—difference in the rate of adverse drug events—as this binary outcome with correlated patient observations required the maximum sample size (appendix 1). For this outcome, we bracketed expected rates of adverse drug events in the control group based on recent Canadian and American studies to be between 10% and 19%. We specified an absolute reduction of 5% as being the smallest clinically relevant difference that would be worthwhile to detect. A difference of this magnitude would conservatively result in 96,000 fewer adverse drug events in Canada annually, at an overall estimated annual cost-savings of \$240million. Specifying an acceptable Type 1 error of 5%, and Type 2 error of 20%, the estimated sample size for the expected range in possible cluster correlations ( $r=0.02-0.05$ ) varies from 2,852 to 4,423 patient admissions, assuming a baseline rate in the control group of 15%, midway between 10% and 19%. Based on an analysis of re-admission rates in 2008, a cluster correlation no greater than 0.03 is expected, which would mean a sample size of 3,376 is required to detect a 5% reduction in adverse drug events. Based on our prior work, we estimate that 10% of patients will not be reached to complete the post-discharge follow-up interview, therefore we estimate that we will need to recruit 3,714 patients to achieve our sample size requirements. Overall, in 2008, there were 17,480 admissions to the MUHC, of which 12,236 were admitted to eligible medical, surgical and psychiatric units. Based on our pilot study, approximately 42% ( $n=5,139$ ) of patients will be eligible for inclusion (i.e. have public drug insurance,  $\geq 18$  years old, first admission in study period, alive at discharge), and of these 3% will refuse to participate, 45% will not be asked for consent because the staff are too busy, and 52% will consent to participate. By providing staff with support to obtain consent from patients, we expect that we can increase the proportion of eligible patients participating to 60%, or 257 per month. Assuming 10 months per year of active recruitment to account for summer and winter holidays, we estimate that it will take 15 months, or approximately 1.5 years to recruit all patients. With an average length of stay of 8.9 days, we can successfully complete enrollment and follow-up in 18-20 months.

*Randomization:* The 28 hospital units will be assigned a random number, stratified by type (medicine, surgery, psychiatry), and the default random number generator in SAS will be used to randomly assign units within stratum to electronically enabled discharge reconciliation or usual care. There will be approximately 1,857 patients who are assigned to medication reconciliation at discharge, 1,857 to usual care.

---

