An intention to treat approach will be used to analyze study results. To determine whether discharge reconciliation reduces the risk of adverse drug events post-discharge, we will use logistic regression within a generalized estimating equation framework to account for clustering of patients within unit. The presence of a probable or definite adverse event (yes vs. no) will be the outcome variable, hospital unit will be the defined clustering factor, and an exchangeable correlation matrix will be used to account for clustering of patients within unit. Discharge reconciliation will be fit as a dummy variable, using usual care as the reference group. We will use the same approach to assess the secondary outcome, ER visits and/or hospital re-admission. For both the primary and secondary outcome, we will assess, whether adjustment for co-interventions and baseline differences between patients in the usual care and intervention arm confound the effect of the intervention. In secondary analysis, we will assess whether the effect of the intervention is modified by hospital unit type (medicine vs. surgery vs. psychiatric), and patient characteristics that are associated with a higher risk of adverse events (age, number of medications at discharge) by including respective interaction terms in the logistic model and testing their significance using the Wald chi-square statistic.

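### The sample size implies 30 patients per cluster, but the trial has 28 units of about 121 evaluable patients: power for 15% to 10% is about 54% at a cluster correlation of 0.03, not 80%

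*Protocol*

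**What the plan says.** All of the sizing is in the sample size paragraph of the protocol's Study Population section.

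- Error rates: "Specifying an acceptable Type 1 error of 5%, and Type 2 error of 20" per cent.
- Control rate: "assuming a baseline rate in the control group of 15%, midway between 10% and 19" per cent.
- Target: "We specified an absolute reduction of 5% as being the smallest clinically relevant difference that would be worthwhile to detect".
- Result: over cluster correlations of 0.02 to 0.05 the required number "varies from 2,852 to 4,423 patient admissions". For the planning value, "a cluster correlation no greater than 0.03 is expected, which would mean a sample size of 3,376 is required to detect a 5% reduction".
- Follow-up: "we estimate that 10% of patients will not be reached to complete the post-discharge follow-up interview", which leads to a recruitment target of 3,714.

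The paragraph gives no number of patients per cluster. It refers to an appendix that is not in the document at hand.

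The cluster itself is defined elsewhere. Study Design lists 16 medical, 10 surgical and 2 psychiatric units. The randomization paragraph says "The 28 hospital units will be assigned a random number, stratified by type (medicine, surgery, psychiatry"), with about 1,857 recruited patients per arm. Data Management and Analysis says "hospital unit will be the defined clustering factor".

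**The concern.** In a cluster trial the inflation over individual randomisation depends on the correlation and on the number of patients per cluster. The three printed totals are enough to work out the cluster size that was used, and it is about a quarter of what 28 units will supply. No smaller cluster is named anywhere: randomisation, the contamination argument in Study Design and the primary model all use the hospital unit. Only the sample size departs from it.

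At stake is the stated 20% type 2 error for the difference that the protocol itself calls the smallest worth detecting. The Expected Contribution section intends the results to inform investment policy and accreditation standards, so readers will rely on that figure when they weigh the result.

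**Working it through.** **Inputs.** Totals of 2,852, 3,376 and 4,423 at r = 0.02, 0.03 and 0.05; control rate 15%, target 10%; 5% type 1 error, taken as two-sided because the protocol does not say and two-sided reproduces its figures; 80% power; 28 units; equal allocation.

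**1. The plan's own figures.** The standard form is N = N0 × [1 + (m − 1)r], with m patients per cluster.

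- Slope: (4,423 − 2,852) / (0.05 − 0.02) = 52,367.
- Intercept: N0 = 2,852 − 0.02 × 52,367 = 1,804.7.
- m − 1 = 52,367 / 1,804.7 = 29.0, so m = 30.

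This step needs no assumption about event rates. N0 can also be identified: the unpooled two-proportion formula for 20% against 15% gives 2 × (1.960 + 0.842)² × (0.16 + 0.1275) / 0.05² = 1,805.2. Multiplying by 1.58, 1.87 and 2.45 returns 2,852, 3,376 and 4,423. All three totals are therefore reproduced with m = 30. At 30 per cluster, 3,376 patients would come from 3,376 / 30 ≈ 113 clusters.

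**2. The design as randomised.** m = 3,376 / 28 = 120.6 evaluable patients per unit. If instead 90% of 3,714 are reached, 3,343 / 28 = 119.4, and the results hardly change.

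**3. Power for 15% to 10%.** Design effect D = 1 + 119.6r; effective number per arm n = 1,688 / D; SE = √[(0.1275 + 0.09) / n]; power = Φ(0.05/SE − 1.96).

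| r | D | n per arm | 0.05/SE | Power, normal | Power, t on 26 df |
|---|---|---|---|---|---|
| 0.01 | 2.20 | 769 | 2.97 | 84% | 82% |
| 0.02 | 3.39 | 498 | 2.39 | 67% | 63% |
| 0.03 | 4.59 | 368 | 2.06 | 54% | 51% |
| 0.05 | 6.98 | 242 | 1.67 | 38-39% | 36% |

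The row for 0.01 lies outside the plan's range and is shown for reference. At r = 0.03 the plan's totals carry a design effect of 1 + 29 × 0.03 = 1.87 instead of 4.59.

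**4. Correlation at which 80% is met.** Without clustering, 15% to 10% needs N0 = 2 × (1.960 + 0.842)² × 0.2175 / 0.05² = 1,366. Solving 3,376 = 1,366 × (1 + 119.6r) gives r = 0.0123.

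**5. Ceiling with 28 units.** As patients per unit grow without limit, n per arm tends to 14 / r. At r = 0.03 this is 467, SE = √(0.2175 / 467) = 0.0216, and power = Φ(2.316 − 1.96) = 64%.

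**6. Detectable difference at r = 0.03.** With n = 368 per arm, 80% power needs a difference of 2.80 SE. For 15% to 8.4%, SE = √[(0.1275 + 0.0769) / 368] = 0.0236, and 2.80 × 0.0236 = 0.066, or 6.6 points.

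**The case against.** **The cluster size is inferred, not printed.** This is so, and the appendix might describe it. But three totals at three correlations fix it at 30, and no appendix text can change what the printed totals imply.

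**0.03 is an upper bound.** The paragraph says no greater than 0.03, and the figure comes from re-admission rates rather than adverse drug events. This stands: 54% is the power at the bound, and a reader should not infer that it is the expected power. At 0.015 it would be 75%. Even so, the plan sized the trial at 0.03, its range begins at 0.02, and power there is 67%.

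**Stratification may help.** If the correlation includes differences between medicine, surgery and psychiatry, the correlation within strata could be lower. The document gives no figure for this, and the primary model as described has no term for unit type.

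**The event rates partly offset the error.** The totals match 20% against 15%, not the stated 15% to 10%, and this makes N larger. The power figures above already credit the trial with all 3,376 patients. Correcting only the rates, at 30 per cluster, would give 1,366 × 1.87 = 2,554 and make the trial look oversized.

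Two stronger readings are tempting and not supported. First, a reader might infer a much steeper loss because units differ in size. The document gives no unit sizes, and the usual correction assumes that patients are weighted equally, whereas an exchangeable working correlation gives patients in large units less weight. With an assumed coefficient of variation of 0.6 and gamma-distributed sizes, power at 0.03 would be about 51% (normal), a loss of about 3 points. Second, a reader might infer that a non-significant result could never exclude a 5-point reduction. That depends on the observed confidence interval, not on design-stage power, and the protocol does not say how a null result will be read.

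**Conclusion.** The sample size statement is wrong as written. The implied 30 patients per cluster cannot be reconciled with 28 units of about 121 evaluable patients, and no other part of the protocol repairs it. The stated 20% type 2 error for a fall from 15% to 10% is not attained at any correlation in the plan's range: the actual figure runs from about 33% at 0.02 to about 61-62% at 0.05, and is about 46% at 0.03.

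These values assume 28 equal units, 3,376 evaluable patients, a two-sided 5% test and a normal approximation; a t reference lowers power by 2 to 4 points. The finding on cluster size depends on none of these assumptions except the standard design-effect formula.

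**What to change.** In the sample size paragraph of Study Population, recompute the design effect with 28 units of about 121 evaluable patients. Replace the claim that 3,376 patients give 20% type 2 error for a 5-point reduction with one of the following:

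- the power for 15% to 10% over correlations of 0.02 to 0.05: about 67% to 39%, and about 54% at 0.03, labelled as assuming equal unit sizes and a normal approximation; or
- the difference detectable with 80% power at 0.03: about 6.6 points (15% to 8.4%).

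State the number of units and patients per unit next to the figures so that they can be reproduced.

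The cost is a rewritten paragraph and a less favourable power statement; it asks for no extra patients or procedures. If the sponsor prefers to keep 80% for 5 points, more patients in the same units will not achieve it at 0.03. It would take more units (about 52 at 121 each: 1,366 × 4.59 ≈ 6,270 patients), a design or analysis that reduces between-unit variance, or a justified correlation of about 0.012 or less.

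### Minor arithmetic error: the 10% non-contact allowance multiplies by 1.10 instead of dividing by 0.90, so 3,714 recruits yield about 3,343 evaluable patients against the 3,376 required

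*Protocol*

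**What the plan says.** The sample-size paragraph (Protocol, Study Population) settles on a cluster correlation of 0.03, "which would mean a sample size of 3,376 is required to detect a 5% reduction in adverse drug events". It then states the expected loss: "we estimate that 10% of patients will not be reached to complete the post-discharge follow-up interview". From these two figures it concludes: "therefore we estimate that we will need to recruit 3,714 patients to achieve our sample size requirements". The Randomization paragraph splits the same total equally: "There will be approximately 1,857 patients who are assigned to medication reconciliation at discharge, 1,857 to usual care".

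Three other places bear on the point:

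- Study Design says that the primary outcome is measured by the interview 30 days after discharge.
- Data Management and Analysis treats patients lost to follow-up as patients whose adverse drug events cannot be measured.
- Outcome Assessment provides for five contact attempts and then a mailed questionnaire for patients who are not reached. It gives no expected return rate.

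**The concern.** A patient who is not interviewed has no primary outcome, so 3,376 must be a count of evaluable patients. The paragraph itself treats it that way by inflating it for non-contact. The inflation, however, adds 10% of the evaluable number, whereas the assumption removes 10% of the recruited number. These are different quantities, and the recruitment target comes out too low for the requirement it is said to meet. The target matters because it is carried into the per-arm numbers and the recruitment timeline. The secondary outcome comes from provincial claims data and does not depend on reaching the patient, so only the primary analysis is affected.

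**Working it through.** **Inputs, all from the Protocol, Study Population.** Required size 3,376; expected non-contact 10%; stated recruitment 3,714 (1,857 per arm); recruitment rate 257 per month; recruitment period 15 months; 28 units; cluster correlation 0.03.

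**1. Reproduce the stated figure.** n × (1 + d) = 3,376 × 1.10 = 3,713.6, rounded up to 3,714. This is an exact match, and 3,714 / 2 = 1,857 matches the per-arm number.

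**2. What 3,714 yields.** N × (1 − d) = 3,714 × 0.90 = 3,342.6, about 3,343. Shortfall: 3,376 − 3,343 = 33, or 1.0%.

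**3. The loss at which 3,714 is just enough.** 1 − 3,376 / 3,714 = 0.091, or 9.1%.

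**4. The number that meets the requirement.** n / (1 − d) = 3,376 / 0.90 = 3,751.1, rounded up to 3,752, or 1,876 per arm. That is 38 more than stated (1.0%). Check: 3,752 × 0.90 = 3,376.8.

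**5. Timeline.** 3,714 / 257 = 14.5 months and 3,752 / 257 = 14.6 months, both within 15. The full period gives 257 × 15 = 3,855 recruits, of whom 3,855 × 0.90 ≈ 3,470 would be evaluable.

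**6. Effect on power.** The available text refers to appendix 1 for the sample size but prints no formula and no cluster size, so this step rests on assumptions. In both versions below, power = Φ(0.05 / SE − 1.96), with SE² = [p₁(1 − p₁) + p₂(1 − p₂)] × 2 × DE / N and design effect DE = 1 + (m − 1) × 0.03. The test is taken as two-sided at 5%.

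- *Inputs inferred because they reproduce 3,376:* 20% against 15% with m = 30 patients per cluster. DE = 1 + 29 × 0.03 = 1.87. N = 3,376 gives 80.0% and N = 3,342.6 gives 79.6%, a loss of 0.4 points.
- *28 units held fixed, so that lost patients shrink the clusters:* m falls from 3,376 / 28 = 120.6 to 3,342.6 / 28 = 119.4, and DE from 4.59 to 4.55. The effective sample size goes from 736 to 734, a drop of about 0.2%. Power changes by about 0.1 point, both for 15% against 10% and for 20% against 15%.

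**7. How the shortcut behaves generally.** Multiplying by (1 + d) and then losing d leaves (1 + d)(1 − d) = 1 − d² of the requirement: 99% at a 10% loss, 96% at a 20% loss.

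**The case against.** The strongest reply is that nothing in the trial turns on this. The 10% and the 3,714 are both offered as estimates, and the per-arm numbers as approximate. A loss of 9.1% instead of 10% would make 3,714 sufficient, and no planning guess is that precise. The mailed questionnaire could also close the gap: about 371 patients would be unreached, and recovering 33 of them (33 / 371 ≈ 9%) would be enough. The recruitment schedule has room for 3,855 patients in any case.

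Most of this stands as a reason to grade the point minor. It does not make the figure right. The sample-size paragraph credits no recovery from the mailing, and no return rate is given. The per-arm wording only repeats half of 3,714. The multiplication by 1.10 explains the printed number exactly, so there is no sign of another derivation.

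A reader might infer that the error leaves the trial short of patients or appreciably underpowered. The documents do not support that: the stated rate and period cover 3,752, and the change in power is a fraction of a point. Nor should the fall from 80.0% to 79.6% be attributed to the plan's own formula. It depends on 20% against 15% and a cluster size of 30. The available text states neither as the design; it gives a 15% control rate with a 5-point reduction.

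The opposite inference, that correcting this figure secures 80% power, is not supported either. The correction only makes the recruitment target consistent with 3,376. Whether 3,376 is itself the right base is a separate question.

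**Conclusion.** The point holds as a minor arithmetic error. On the protocol's own 10% loss, 3,714 recruits leave about 3,343 evaluable patients, 33 (1%) fewer than the 3,376 it states as required. The consistent target is 3,752. This conclusion needs only the two printed inputs and the reading that the 10% applies to recruited patients, which is how the sentence is written. The power effect is well under one percentage point under either set of assumptions above, and the timeline does not change.

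**What to change.** In the sample-size paragraph, restate the recruitment figure as 3,376 / 0.90 = 3,752, and in the Randomization paragraph restate the arms as 1,876 each. Alternatively, keep 3,714 and 1,857 and say that at 10% non-contact they yield about 3,343 evaluable patients. If the base size is revised for any other reason, divide the new figure by 0.90 rather than multiplying it by 1.10.

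The cost is two corrected numbers or one added sentence. The restated target means 38 more recruits, about 0.15 of a month at 257 per month (38 / 257), within the 15 months already planned.
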